### **6.3.2. Subgroup Analyses of the Primary Outcomes**

For each of the two primary outcomes, Hazard ratios of the treatment in the following subgroups will be estimated using the Cox proportional hazard models, and differences in the HRs among the subgroups tested by the ANOVA test. The subgroups include:

- (1) Age (<35 years, ≥35 years)
- (2) Gender (male, female)
- (3) Hypertensive (yes, no)
- (4) baseline 24-hour UPE (<1.5 g/day, ≥1.5 g/day)
- (5) baseline eGFR (<50 or ≥50ml/min /1.73m^2)
- (6) Individual MESTC scores (M0, M1; E0, E1; S0, S1; C0, C1, C2; T0, T1, T2)

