## 5. Rationale and background

Immunoglobulin A (IgA) nephropathy is the most common type of glomerulonephritis. Up to 40% of patients with IgA nephropathy progress to end stage renal disease (ESRD) over 10 to 20 years, making it the leading cause of kidney failure in many parts of the world.

The appropriate therapy of IgA nephropathy remains uncertain. The central role of the immune and autoimmune activation in the pathogenesis of IgA nephropathy indicates a potential benefit of immunosuppression for treating the disease. However, the efficacy of immunosuppression in IgA nephropathy have not yielded confirmed results. Current management of IgA nephropathy remains focused on non-immunosuppressive-based strategies, so-called supportive care, to reduce proteinuria and slow the disease progression. This encompasses optimal inhibition of renin-angiotensin system (RAS), rigorous blood pressure control, and lifestyle modification. However, despite intensive supportive care, considerable number of patients still have massive proteinuria and remain at high risk of disease progression. The Kidney Disease Improving Global Outcomes (KDIGO) guidelines suggest the use of systemic glucocorticoids in patients who have a proteinuria level above 1g per day and an estimated glomerular filtration rate (eGFR) higher than 50ml per minutes per 1.73m^2, despite of 3 to 6 months of optimized supportive care. The benefits of immunosuppressive therapy, particularly in those with an eGFR < 50 ml/min/1.73m^2, remain largely unclear.

Mycophenolate mofetil (MMF) is a potent immunosuppressive agent which is relative selective for lymphocytes and inhibits antibody production by B cells stronger than any other immunosuppressants. However, data regarding the efficacy of MMF treatment in patients with IgA nephropathy are controversial, probably due to the small sample size in most published studies, and differences in patients characteristics, e.g. low or high risk of disease progression, and with or without consistent blockade of RAS.

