## **6.3. Efficacy Analyses**

### **6.3.1. Main Analyses of the Primary Outcomes**

- The number of the composite outcome (primary outcome 1) and its components by each treatment group in ITT.
- The number of disease progression (primary outcome 2) by each treatment group in ITT.
- Kaplan-Meier curves of cumulative survival rates of the two primary outcomes by two treatment groups in ITT.
- To perform log-rank tests on the two primary outcomes between the two treatment groups in ITT. A p-value of 0.025 will be regarded as statistically significant.
- Estimate the hazard ratios (and 95% confidence intervals) of the treatment for the two primary outcomes, respectively, using the Cox proportional hazard models, with and without covariate adjustment. The adjusting covariates include age, sex, BMI, SBP, eGFR, logarithm of UPE rate and individual Oxford MEST-C scores at baseline.

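### Whether the MMF effect varies with age, proteinuria or eGFR is tested only across a two-group cut, which loses about a third of the information on a gradual change if the cut lies near the median

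*Combined protocol and SAP*

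**What the plan says.** SAP 6.3.2 covers both primary outcomes and states that "Hazard ratios of the treatment in the following subgroups will be estimated using the Cox proportional hazard models". Its subgroup list includes "1) Age (<35 years, ≥35 years", "4) baseline 24-hour UPE (<1.5 g/day, ≥1.5 g/day" and "baseline eGFR (<50 or ≥50ml/min", each a two-group factor. Effect modification is to be judged by "differences in the HRs among the subgroups tested by the ANOVA test".

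SAP 6.3.1 specifies the adjusted Cox model for the same outcomes: "The adjusting covariates include age, sex, BMI, SBP, eGFR, logarithm of UPE rate and individual Oxford MEST-C scores at baseline". No categories are given there for age or eGFR, and UPE enters as a logarithm. These variables are adjusters only. Neither document plans a product term between treatment and a continuous variable.

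Protocol 7.12 lists possible subgroup factors. It also cuts eGFR at 50, but cuts proteinuria at 1.0 g/day. No power is stated for any subgroup comparison. SAP 4.4 sets significance levels for the primary, secondary and safety analyses and names none for subgroup tests.

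**The concern.** A two-group comparison treats all patients on one side of the cut as alike. An eGFR of 31 counts the same as 49, while 49 and 51 count as different. If the benefit of MMF rises or falls steadily with one of these variables, the variation within each side carries information that the comparison does not use.

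The trial has few events to spare. At the planning rates about 13 events are expected on MMF, so any two-way split leaves at least one MMF subgroup with six or fewer. The uncut values are collected anyway and, for UPE at least, are already modelled uncut. The result also depends on where the cut falls, and the proteinuria cut differs between the protocol's provisional list and the SAP.

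At stake is the sensitivity of a secondary look at effect modification. The primary comparisons are not affected. The point is also separate from which statistic compares the subgroup hazard ratios: correcting that statistic would leave the variables cut in two.

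**Working it through.** **Inputs from the documents.** Three-year event rates 36% (control) and 16% (MMF), 80% power, two-sided 0.05, 76 per group, 84 per group after 10% loss (Protocol 7.4); 1:1 allocation (Protocol 7.5); the cuts in SAP 6.3.2.

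**Assumptions.** Interaction tested at two-sided 0.05. Modifier normally distributed unless stated. Log hazard ratio linear in the modifier. Gradient sizes are illustrative.

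**1. The plan's own figure.** For two proportions with pooled variance and no continuity correction, the mean rate is 0.26 and

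n = [1.96√(2 × 0.26 × 0.74) + 0.842√(0.36 × 0.64 + 0.16 × 0.84)]² / 0.20² = 74.3, so 75 per group.

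The plan's 76 gives 80.9% power, so its figure is reproduced to within one patient. 76 × 1.10 = 83.6, which gives 84.

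**2. Expected events.** 84 × 0.36 + 84 × 0.16 = 30.2 + 13.4 = 43.7, about 44. The planning hazard ratio is ln(0.84)/ln(0.64) = 0.391.

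**3. Information kept by a cut.** For a linear interaction, the efficiency of a two-group version relative to the continuous one is the squared correlation between the modifier and its dichotomised form:

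E = φ(c)² / [p(1 − p)], where p is the share below the cut c.

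At the median, E = 0.1592/0.25 = 0.637, a loss of 36%. The interaction z is multiplied by √E = 0.798. For a test with 80% power, z = 1.960 + 0.842 = 2.802; then 2.802 × 0.798 = 2.235, and Φ(2.235 − 1.960) = 61%.

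| Share on the smaller side | E | 80% power becomes | 50% power becomes |
|---|---|---|---|
| 50% | 0.64 | 61% | 35% |
| 30% | 0.58 | 57% | 32% |
| 20% | 0.49 | 50% | 28% |
| 10% | 0.34 | 37% | 21% |

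**4. Where the SAP cuts might fall.** The documents give no distribution. Assumed shapes (UPE lognormal within 0.75-3.5 g/day, eGFR truncated at 30, age from 18) that put 25% to 67% of patients below the cuts give E of about 0.51 to 0.70. That is a relative power loss of about 20% to 43%.

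**5. Check by simulation at the trial's size.** Cox models with interaction tests: 84 per arm, control risk 36%, hazard ratio 0.391 at the modifier mean, 10% loss, about 42-49 events, several hundred replicates per setting.

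| Change in log HR per SD | Cut | Continuous | Two groups |
|---|---|---|---|
| 0.4 | median | 22% | 15% |
| 0.5 | median | 33% | 23% |
| 0.7 | median | 57-60% | 39-40% |
| 1.0 | median | 86% | 63% |
| 0.4 | 20/80 | 22% | 11% |
| 0.7 | 20/80 | 55% | 27% |

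In the 20/80 rows, 8-9% of runs were dropped because the fit failed. With a modifier that is itself prognostic (0.5 per SD, either direction), median-split ratios of two-group to continuous power went down to 0.59. With a prognostic modifier cut at the 30th percentile, power fell from 34% to 18% and from 61% to 28%.

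**6. The reverse case.** If the effect jumps exactly at the cut, the two-group test is better: 31% against 20% in one simulated setting.

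**The case against.** The strongest objection concerns eGFR. The rationale in Protocol 5 reads "The benefits of immunosuppressive therapy, particularly in those with an eGFR" and continues with the below-50 threshold, which matches the guideline criterion cited just before it. The planned split at 50 answers that question as posed, and a true step there favours the split. This stands. A reader might infer that the split cannot address the trial's motivating question, but the text does not support that, and the cut at 50 should stay.

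Second, power is poor whichever coding is used. For a hazard-ratio ratio of about 1.5 per SD the continuous test has only about 22%. Even 0.7 per SD, which moves the hazard ratio from about 0.19 at −1 SD to 0.79 at +1 SD, is detected little more than half the time. This also stands. The number of events limits the analysis more than the coding does, and a null result would be uninformative either way.

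Third, pre-specified clinical cut-points are ordinary practice, SAP 4.1 allows for clinically meaningful categories, and a continuous term adds a linearity assumption. That supports keeping the subgroup display. It does not weigh against adding a more efficient test beside it.

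Two stronger readings are tempting. One is that cutting halves the power in general. That requires a lopsided cut, or an off-median cut with a prognostic modifier, and the documents show neither. The other is that a missed gradient would be reported as a uniform effect. The documents contain no rule for reporting a non-significant subgroup test that way.

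**Conclusion.** The point holds as a cheap improvement and is not an error in the plan. For age, UPE and eGFR the SAP relies solely on two-group comparisons. Against a gradual change in effect, a cut near the median costs about 36% of the information and about a quarter to 40% of the power, and a cut far from the median costs more. These sizes rest on a linear log hazard ratio, a 0.05 level, the planning event rates and assumed modifier distributions and gradients. The loss at the actual cuts cannot be computed from the documents. The recommended test would recover the lost information but would not make the interaction analysis well powered.

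**What to change.** Leave the SAP 6.3.2 subgroup hazard ratios and their between-group comparison as they are, including eGFR below 50 against 50 or above. Add a sentence along these lines: for age, baseline eGFR and log baseline UPE, a Cox model with treatment, the continuous variable and their product will give a 1-df interaction test, and the fitted hazard ratio with its 95% band will be plotted over the observed range; these analyses are exploratory.

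The cost is that wording and one extra model per variable for each primary outcome. No new data are needed and the primary analysis is unchanged. The price is the linearity assumption, and lower power than the split if the true change is a step at the cut. Reporting both covers each case.

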### **6.3.3. Analysis of the Secondary Outcomes**

#### **6.3.3.1. The Time to 30% Reduction in eGFR**

- The number of patients reached 30% reduction in eGFR by each treatment group in ITT.
- Kaplan-Meier curves of cumulative survival rate of the outcome by two treatment groups in ITT.
- Perform log rank tests on the outcomes between the two treatment groups in ITT.

- Estimate the hazard ratios (and 95% confidence intervals) of the treatment using the Cox proportional hazard models, with and without covariate adjustment. The adjusting covariates include age, sex, BMI, SBP, eGFR, logarithm of UPE rate and individual Oxford MEST-C scores at baseline.

#### **6.3.3.2. Annual Absolute Change in eGFR (eGFR Slope)**

The eGFR slope of each participant in ITT during the trial period will be estimated using a linear mixed effect model with random intercept and random slope. The difference in the eGFR slope between the two treatment groups will be estimated and tested using a linear mixed effect model with an interaction term between treatment group and time.

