#### 7.5 Randomization

All participants meeting inclusion and exclusion criteria and providing informed consent will be randomized to either the MMF plus supportive care group or supportive care alone group in a 1:1 ratio. A random sequence with a block size of 6 will be generated before the start of the trial and maintained by a party not involved in the conduct of the study. Randomization will be carried out via phone call.

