#### **Inclusion criteria for randomization:**

UPE remained at 0.75-3.5 g per day at the end of run-in period

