#### **6.3.3.3. Rapid Renal Function Decline (eGFR Slope < -5 ml/min/1.73m^2/year)**

Tabulate the number of participants with an estimated eGFR slope < -5 ml/min/1.73m^2/year stratified by treatment group. Difference in the event rate between the treatment groups is tested using logistic regression analysis, with and without covariate adjustment. The adjusting covariates include age, sex, BMI, SBP, eGFR, logarithm of UPE rate and individual Oxford MEST-C scores at baseline. ORs and the confidence intervals will be reported.

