#### **6.3.3.4. Percentage Changes in the Rate of Urinary Protein Excretion Rate**

The baseline 24-hour UPE is calculated as the mean of the two 24-hour UPE value from Visit 4 (pre-randomization visit) and Visit 5 (randomization visit). The 24-hour UPE at exit is calculated as the mean of from the last two visits before study exit. Percentage change is calculated as 100% x (exit value-baseline)/baseline. The difference in the percentage change between the two treatment groups will be tested using unpaired two-sample t-test.

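### The eGFR-slope comparison names no baseline covariate; adding baseline log UPE and its interaction with time could give a modest, conditional gain in precision

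*Combined protocol and SAP*

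**What the plan says.** SAP 6.3.3.2 has two sentences. Each patient's slope is "estimated using a linear mixed effect model with random intercept and random slope". The between-arm difference is then "estimated and tested using a linear mixed effect model with an interaction term between treatment group and time". The second sentence names no baseline covariate and does not restate the random effects.

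The related outcomes are handled differently:

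- **Both primary outcomes (SAP 6.3.1):** unadjusted log-rank tests, then hazard ratios "using the Cox proportional hazard models, with and without covariate adjustment".
- **Time to 30% eGFR reduction (SAP 6.3.3.1):** Cox models with and without a covariate list that includes "logarithm of UPE rate and individual Oxford MEST-C scores at baseline".
- **Rapid decline (SAP 6.3.3.3):** logistic regression with and without adjustment. "The adjusting covariates include age, sex, BMI, SBP, eGFR, logarithm of UPE rate and individual Oxford MEST-C scores at baseline".

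On allocation, Protocol 7.5 says "A random sequence with a block size of 6 will be generated before the start of the trial" and names no stratification factor. A UPE value at the end of run-in is needed to randomise (SAP 3.1: "UPE remained at 0.75-3.5 g per day at the end of run-in period"). SAP 6.3.3.4 defines the baseline: "The baseline 24-hour UPE is calculated as the mean of the two 24-hour UPE value from Visit 4" and Visit 5.

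**The concern.** Rapid decline is the fitted slope cut at −5 ml/min/1.73m² per year. The dichotomised outcome therefore gets an adjusted analysis, while the continuous slope behind it gets none. Neither document gives a reason.

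The documents themselves treat proteinuria as a marker of progression risk. The background sections link persistent proteinuria to high risk, eligibility depends on it, and SAP 6.3.2 uses it as a subgroup factor. If baseline UPE predicts the rate of eGFR loss among randomised patients, part of the between-patient variation in slope is explainable. The present model leaves that part in the error of the treatment-by-time term, so the interval is wider than it need be.

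**Working it through.** **1. The plan's own figure.** Protocol 7.4 sizes the composite outcome only: 36% against 16%, two-sided 0.05, 80% power. With pooled variance and no continuity correction, n = [1.96·√(2·0.26·0.74) + 0.842·√(0.36·0.64 + 0.16·0.84)]² / 0.20² = (1.216 + 0.508)² / 0.04 = 74.3, so 75 per group. The stated 76 gives 80.9% power. The figure reproduces, but it says nothing about the slope, for which no power is claimed.

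**2. Inputs for the slope.**
- From the documents: two-sided 0.05 for secondary outcomes (SAP 4.4); 24 creatinine visits from week 0 to week 156 (Table 1), for which Sxx = Σ(t − t̄)² = 21.4 years²; 76 per arm.
- Assumed, because neither document gives them: between-patient slope SD 4 ml/min/1.73m² per year; residual SD 5 ml/min/1.73m²; random intercept and slope in the comparison model; all visits attended; correlation ρ between baseline log UPE and slope from 0.1 to 0.5.

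**3. Unadjusted standard error.** The variance of one patient's fitted slope is 4² + 5²/21.4 = 16 + 1.17 = 17.17. Between-patient variation is 16/17.17 = 93% of it. SE = √(2 × 17.17/76) = 0.672.

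**4. Adjusted standard error.** Baseline log UPE × time multiplies the between-patient part by (1 − ρ²). For a slope difference with 80% power unadjusted (2.80 × SE₀), power = Φ(2.80 × SE₀/SE₁ − 1.96).

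| ρ | ρ² | SE₁ | Power |
|---|---|---|---|
| 0 | 0 | 0.672 | 80.0% |
| 0.1 | 0.01 | 0.669 | 80.4% |
| 0.2 | 0.04 | 0.660 | 81.5% |
| 0.3 | 0.09 | 0.643 | 83.3% |
| 0.4 | 0.16 | 0.620 | 85.9% |
| 0.5 | 0.25 | 0.589 | 89.2% |

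**5. Sensitivity to the variance components.** At ρ² = 0.15 (ρ about 0.39), slope SD 4 with residual SD 5 gives 85.6%. Slope SD 3 with residual SD 8 gives 84.5%, slope SD 3 with residual SD 10 gives 83.9%, and slope SD 2 with residual SD 8 gives 83.4%. The gain shrinks as residual variation grows relative to slope SD.

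**6. Main effect alone.** With 84 per arm, slope SD 5, residual SD 4, intercept SD 14 and intercept–slope correlation 0.2, the generalised least squares SE of treatment × time is 0.783 with no covariate and 0.783 with log UPE as a main effect. With log UPE × time added it is 0.750 at ρ = 0.3. All the gain comes from the interaction with time.

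**7. Chance imbalance.** At ρ² = 0.15 and 84 per arm, an imbalance in mean log UPE of one standard error of the between-arm difference corresponds to √0.15 × 4 × √(2/84) = 0.24 ml/min/1.73m² per year. The unadjusted SE at 84 per arm is √(2 × 17.17/84) = 0.639. Since 0.24²/0.639² = 0.14 = 0.15 × 0.93, this imbalance is exactly the part of the unadjusted variance that adjustment removes. It is already inside the standard error. A full one-SD difference in log UPE between arms would correspond to √0.15 × 4 = 1.55, but that is 1/√(2/84) = 6.5 standard errors of the difference in means.

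**The case against.** The strongest reply is that nothing is wrong. Randomisation makes the unadjusted treatment-by-time test valid, the slope is a secondary outcome, and the plan promises no power for it. All of this stands.

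The size of the gain also rests wholly on assumption. Selecting high-risk patients on proteinuria does not show that UPE predicts slope within the selected group, and the 0.75–3.5 g/day window at randomisation may weaken the correlation. At ρ of 0.1 to 0.2 the gain is only 0.4 to 1.5 points. A gain of 5 points needs ρ of about 0.39 under the assumptions above, and no section supports that value.

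A reader might infer three stronger things, and the documents do not support them:

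- **That the slope estimate is biased, or that power is certainly being thrown away.** The test is valid, and the loss depends on a correlation that is not given.
- **That the SAP makes adjustment its main analysis everywhere else.** The primary tests are unadjusted log-rank tests, and the Cox and logistic models are reported both ways.
- **That chance imbalance in proteinuria is a further cost on top of lost precision.** Step 7 shows that it is the same variance counted again.

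A covariate-by-time term also appears in no other SAP model, so making the adjusted model the main one is a choice for the sponsor. What survives is that the slope is the one related outcome without an adjusted analysis, and that adding one is cheap.

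**Conclusion.** The point holds as an optional improvement in efficiency to a secondary analysis. The slope comparison omits a baseline variable that is already collected and already used as a covariate for the related outcomes, and allocation does nothing to balance it. The benefit is modest and conditional: from 80% power, about 0.4 points at ρ = 0.1, 3.3 at ρ = 0.3 and 9.2 at ρ = 0.5, with slope SD 4, residual SD 5, complete visits, and random intercept and slope in the comparison model. That last item is an inference, because SAP 6.3.3.2 states the random effects only for estimating individual slopes. The documents cannot say where in this range the trial lies.

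**What to change.** Before database lock, amend SAP 6.3.3.2 as follows:

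1. Add baseline log UPE and baseline log UPE × time as fixed effects to the treatment-by-time mixed model. A main effect alone is not enough.
2. State that the comparison model keeps the random intercept and random slope.
3. Report this model together with the unadjusted one, and prespecify which of the two is the main slope result, so that the choice cannot follow the data.

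The cost is two model parameters in about 168 patients. One reconciliation must come first: SAP 6.3.3.4 averages UPE from Visits 4 and 5, Table 1 in both documents shows no 24-hour urine protein at Visit 4, and Protocol 7.10 says the collection is made at every visit. The SAP's existing adjusted models use baseline UPE too, so this has to be settled anyway.

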#### **6.3.3.3. Rapid Renal Function Decline (eGFR Slope < -5 ml/min/1.73m^2/year)**

Tabulate the number of participants with an estimated eGFR slope < -5 ml/min/1.73m^2/year stratified by treatment group. Difference in the event rate between the treatment groups is tested using logistic regression analysis, with and without covariate adjustment. The adjusting covariates include age, sex, BMI, SBP, eGFR, logarithm of UPE rate and individual Oxford MEST-C scores at baseline. ORs and the confidence intervals will be reported.

#### **6.3.3.4. Percentage Changes in the Rate of Urinary Protein Excretion Rate**

The baseline 24-hour UPE is calculated as the mean of the two 24-hour UPE value from Visit 4 (pre-randomization visit) and Visit 5 (randomization visit). The 24-hour UPE at exit is calculated as the mean of from the last two visits before study exit. Percentage change is calculated as 100% x (exit value-baseline)/baseline. The difference in the percentage change between the two treatment groups will be tested using unpaired two-sample t-test.

